## Abstract

**Aim of the study:**

Intraductal papillary mucinous neoplasms (IPMNs) are among the most common cystic pancreatic neoplasms, with a potential to progress to malignancy. The increasing prevalence of IPMNs, coupled with the widespread use of GLP-1 receptor agonists (GLP-1 RAs) for diabetes and obesity management, raises concerns about the safety of these medications in patients with preexisting pancreatic conditions. Despite their proven metabolic benefits, questions remain about their impact on pancreatic pathology. This study investigates the association between GLP-1 RA use and IPMN progression to address this critical gap in the current literature.

**Methods:**

This retrospective multicentric cohort study will analyse data from January 2010 to July 2026 across three Swiss tertiary institutions. Patients with a radiological diagnosis of IPMN and/or treated with GLP-1 RAs will be included. Patients will be stratified into four groups according to a 2 × 2 design based on GLP-1 RAs exposure and IPMN status. The primary objective is to evaluate the impact of GLP-1 RAs on IPMN progression using radiological criteria from the Kyoto 2023 Consensus. Secondary objectives include assessing changes in tumour markers (CA19−9, CEA), the incidence of acute pancreatitis, the progression of IPMNs to high-grade dysplasia or invasive carcinoma, and the need for surgical intervention or altered surveillance protocols associated with GLP1 RAs use.

**Discussion:**

This study aims to explore potential associations between GLP-1 RA use and changes in IPMN characteristics, tumour markers, and disease progression. Given the retrospective design and expected small sample size (estimated at 30–60 patients in total), the study may not be powered to establish definitive correlations. Nonetheless, it will generate preliminary data to help inform hypotheses and guide future research. Any observed trends could provide valuable insights into the safety of GLP-1 RAs in patients with IPMNs and contribute to more informed clinical decision-making regarding the use of these agents in a population at risk for pancreatic disease progression.

**Trial registration:**

ClinicalTrials.gov NCT07014709

## Introduction

Intraductal papillary mucinous neoplasms (IPMNs) are among the most common cystic pancreatic neoplasms, notable for their potential to progress to malignancy, particularly in main-duct subtypes [1–3]. The incidence of IPMNs has risen significantly, partly due to advancements in imaging technology [4]. Chronic pancreatitis is recognized as a relevant risk factor for the development of IPMN, likely due to the inflammatory changes that alter the pancreatic ductal epithelium [5,6].

The widespread adoption of Glucagon-like peptide-1 receptor agonists (GLP-1 RAs) for diabetes since 2005 and more recently obesity management has raised questions about their safety in patients with preexisting pancreatic conditions. While GLP-1 RAs are effective in promoting weight loss and metabolic improvement, concerns about their potential links to acute pancreatitis (AP) and pancreatic cancer remain unresolved. Although recent meta-analyses [7,8] have not demonstrated a definitive association between GLP-1 RAs and acute pancreatitis, no study specifically addressed their safety in patients with preexisting IPMNs.

The relationship between GLP-1 RAs and pancreatic cancer remains uncertain. While recent meta-analyses [9,10] have not demonstrated a definitive association between GLP-1 RAs use and pancreatic cancer, pharmacovigilance data have suggested a potential signal, with an increased reporting rate of pancreatic malignant neoplasms in association with GLP-1 RAs exposure. The definitive mechanism underlying a potential association between GLP-1 RAs and pancreatic neoplasia has not been established. Proposed hypotheses include a possible link mediated through pancreatitis, a known risk factor for pancreatic cancer, as well as experimental data suggesting potential pro-inflammatory and proliferative effects within pancreatic tissue. However, these findings are inconsistent across studies, and no causal mechanism has been confirmed. [11,12]

## Methods

### Study design

This is a retrospective multicentric cohort study conducted at three Swiss Hospitals, Cantonal Hospital of Fribourg (HFR), University Hospital of Geneva (HUG) and University Hospital of Bern (Inselspital), to evaluate the effects of GLP-1 RA therapy on patients with IPMNs. Data from January 2010 to July 2026 will be reviewed.

The primary focus of the study will be to investigate the impact of GLP-1 RA therapy on the progression of IPMNs, specifically examining changes in IPMN radiological characteristics such as described in the Kyoto 2023 Consensus [1]. Additionally, the study will assess the variations in serum tumor markers such as CA19−9 and CEA and incidence of acute pancreatitis in patients undergoing GLP-1 RA treatment. The progression of IPMNs to high-grade dysplasia or invasive carcinoma, the need for surgical intervention or changes in IPMN surveillance protocols will also be assessed.

Data already collected from medical records, laboratory results, and imaging studies will be reviewed for patients diagnosed with IPMNs and treated with GLP-1 RAs for diabetes or obesity between 01.01.2010 and 31.07.2025 at HFR, HUG, and Inselspital. To assess the impact of GLP-1 RA exposure in patients with IPMNs, we will also include control groups without GLP-1 RA exposure and without IPMNs, resulting in four groups defined by a 2 × 2 factorial design (GLP-1 RA exposure: yes/no × IPMN: yes/no) (Fig 1).

**Fig 1 pone.0357577.g001:**
[figure not shown]
Study design and comparison groups. Schematic overview of the retrospective multicentric cohort study evaluating the impact of GLP-1 RA therapy on patients with IPMNs. Four study groups will be included according to IPMN diagnosis and GLP-1 RA exposure: patients with IPMN treated with GLP-1 RAs, patients with IPMN not treated with GLP-1 RAs, patients without IPMN treated with GLP-1 RAs, and patients without IPMN and without GLP-1 RA exposure (general population). The primary outcome (1) is the progression of radiological IPMN characteristics according to the Kyoto 2023 Consensus criteria. Secondary outcomes include longitudinal changes in serum CA19−9 and CEA levels (2) and the incidence of acute pancreatitis (3). We hypothesize that GLP-1 RA therapy is not associated with an increased progression of IPMN radiological features or adverse pancreatic outcomes compared with patients not exposed to GLP-1 RAs.

A list of patients diagnosed with IPMNs will be compiled (List A), and this group will then be cross-referenced with data from patients who have been treated with GLP-1 RAs (List B). ICD-10 codes, keywords like IPMN and ATC medication codes will be used to identify the patients and compile the two lists (S1 File). This method will allow us to identify the subset of patients in whom both IPMN and GLP-1 RA treatment are present. The same number of patients will be randomly extracted from the two lists. For example, if 3 patients with GLP1-RA and IPMN are extracted in the HFR dataset, then 3 patients will be extracted in List A and 3 in List B. The same procedure will be carried out for the other two institutions. For the no GLP-1 RA & no IPMN group, the proportion of AP will be generalized to the incidence in the general population.

Evaluation methods will include a review of medical records for demographic data (age, sex, BMI), clinical and family history, and comorbidities (diabetes, dyslipedmia, hypertension), along with laboratory values (lipase, amylase, HbA1c, fasting glucose, HOMA-IR, plasma insulin, C-peptide, CEA, CA 19−9). Radiological data, including data from MRI scans, will be used to monitor changes in IPMN characteristics. If only CT scans are available, they will also be evaluated, even if this is not the preferred imaging method for IPMN evaluation. Gastroenterological examination including EUS and cytological results will also be reviewed. This study adheres to the SPIRIT 2013 recommendations.

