### Hypotesis

Our Hypothesis are illustrated in Fig 1.

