### Sample size and statistical analysis

#### Sampling plan.

The sample size is expected to be between 10 and 20 patients for the condition with GLP-1 RAs and IPMN, due to the rare nature of the patient population with both IPMN and GLP-1 RA use. The other conditions (GLP-1 RA & no-IPMN, no GLP-1 RA & IPMN) will match in sample size the above-mentioned condition as it is the most stringent. This design ensures to isolate the interaction effect of GLP-1 RA and IPMN while ensuring proper statistical power. Indeed, a-priori power analysis computed with G*Power [22] shows that for our smallest estimation of effect size (i.e., 10–30 patients per condition, 30–60 in total), a 2x2 ANOVA detects a significant medium effect size with a power if 80% and an alpha of 0.05.

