#### Analysis plan.

H1) We expect significantly more occurrences of change in at least one of the criteria from the Kyoto 2023 Consensus (see Outcomes section) [1] from patients with GLP-1 RA & IPMN than patients with no GLP-1 RA & IPMN, as assessed by a one-sided test of two proportions. H2) We expect significantly greater changes in the CEA (H2a) and CA19−9 (H2b) serum tumor markers over time induced by GLP-1 RA, as assessed by the interaction term of the within-factor Time and the between-factor Group (GLP-1 RA & IPMN vs. no GLP-1 RA & IPMN). H3) We expect significantly different incidence of AP driven by GLP-1 RA and IPMN, as assessed by a Chi-square test across all conditions (GLP-1 RA & IPMN, no GLP-1 RA & IPMN, GLP-1 RA & no IPMN).

Timing of progression: T0 will be defined as the first available follow-up examination for patients with IPMN who were not treated with GLP-1 RAs, and as the first available follow-up examination after initiation of GLP-1 RA therapy for patients with IPMN who received GLP-1 RAs.

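### The Fig 1 caption and H1 predict opposite results for the primary outcome, and the planned one-sided test cannot support the caption's version

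*Protocol article*

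**What the plan says.** The hypothesis section of the protocol article is a single sentence: "Our Hypothesis are illustrated in Fig 1". The Fig 1 caption, under Study design, names radiological progression by the Kyoto 2023 criteria as the primary outcome, and marker changes and acute pancreatitis (AP) as secondary outcomes. It then states: "We hypothesize that GLP-1 RA therapy is not associated with an increased progression of IPMN radiological features or adverse pancreatic outcomes", the comparison being with unexposed patients.

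The Analysis plan gives three expectations:

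- **H1 (primary outcome):** "We expect significantly more occurrences of change in at least one of the criteria from the Kyoto 2023 Consensus" in IPMN patients on a GLP-1 RA than in IPMN patients not on one, "as assessed by a one-sided test of two proportions".
- **H2:** larger changes in CEA and CA19-9, described as changes in "serum tumor markers over time induced by GLP-1 RA", judged by a time-by-group interaction.
- **H3:** "We expect significantly different incidence of AP driven by GLP-1 RA and IPMN", by a chi-square test across three groups.

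On size, the Sampling plan says: "The sample size is expected to be between 10 and 20 patients for the condition with GLP-1 RAs and IPMN", with the other sampled groups matched to it. The Discussion parts of the abstract and of the main text both caution that power may be limited and that the results serve to generate hypotheses.

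**The concern.** Both statements are framed as the investigators' own prediction, and neither is labelled as a null hypothesis. For the primary outcome they point in opposite directions. A significant H1 test would agree with the Analysis plan and a non-significant one with the caption, so a pre-stated prediction would be available for either result. Fixing the direction of the main claim in advance is a central purpose of publishing a protocol.

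The caption's statement is also the null of the planned test, and failing to reject a null does not establish it. With groups this small, non-significance is likely even if progression truly increases. In a drug-safety question, that result could be taken as reassurance that the data do not give.

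**Working it through.** **Step 1. Compare the statements, hypothesis by hypothesis.**

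| | Fig 1 caption | Analysis plan | Relation |
|---|---|---|---|
| Radiological progression | no increase | H1: significantly more, one-sided | direct contradiction |
| Tumour markers | not named in the hypothesis sentence | H2: greater change | not clearly covered |
| AP | no increase in adverse pancreatic outcomes | H3: incidence differs, no direction, three groups | tension, not opposition |

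Only H1 is the direct opposite of the caption. This step needs no numbers.

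**Step 2. What the H1 test can show.** Let p1 and p0 be the risks in exposed and unexposed IPMN patients. The test has null p1 ≤ p0 and alternative p1 > p0. The caption asserts p1 ≤ p0, which is the null.

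**Step 3. The plan's own power figure.** The Sampling plan says that "a 2x2 ANOVA detects a significant medium effect size with a power if 80% and an alpha of 0.05", for 30 to 60 patients in total. This refers to an ANOVA, not to the H1 test. Taking medium as Cohen's f = 0.25 (assumed; the article gives no number), a between-subjects 2×2 ANOVA with noncentrality f²N has power 26% at N = 30 and 48% at N = 60; 80% needs N = 128. A mixed group-by-time design with an assumed correlation of 0.5 reaches 80% at N = 34. Neither calculation says how informative a non-significant H1 result would be.

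**Step 4. How often H1 would be non-significant when risk truly rises.** The inputs are 10 or 20 per group (Sampling plan) and one-sided alpha 0.05 (the Sampling plan's alpha, assumed to apply to H1). The risks are assumed, because the documents give none. The method is exact binomial enumeration of the pooled z-test.

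| Assumed p0 → p1 | Non-significant, n = 10 | Non-significant, n = 20 |
|---|---|---|
| 10% → 20% | 87.4% | 77.2% |
| 10% → 30% | 71.7% | 51.1% |
| 20% → 40% | 75.0% | 59.3% |
| 30% → 50% | 75.2% | 65.5% |

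Normal-approximation check for 20% → 40%, with mean risk 0.30: power = Φ{[0.20 − 1.645·√(2·0.30·0.70/n)] / √[(0.20·0.80 + 0.40·0.60)/n]}. At n = 10 this is Φ(−0.137/0.200) = 24.7%, and at n = 20 it is Φ(−0.038/0.141) = 39.3%. Both agree with the table. Fisher's exact test gives lower power, 13% and 29%.

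**Step 5. What an apparently null result leaves open.** Take equal observed risks of 20%. The Newcombe 95% limits are ±√[(u − 0.20)² + (0.20 − l)²], where l and u are the Wilson limits.

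- 2/10 vs 2/10: l = 0.057, u = 0.510, so ±√(0.310² + 0.143²) = ±0.341.
- 4/20 vs 4/20: l = 0.081, u = 0.416, so ±√(0.216² + 0.119²) = ±0.247.

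**Step 6. What testing the caption's hypothesis would need.** For non-inferiority with equal true risks p, margin m, one-sided 0.05 and 80% power, n per group = (1.645 + 0.842)²·2p(1 − p)/m². The margins are assumed.

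| Margin | p = 10% | p = 20% | p = 30% |
|---|---|---|---|
| 20 points | 28 | 50 | 65 |
| 10 points | 112 | 198 | 260 |

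Every entry exceeds the planned 10 to 20 per group.

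**The case against.** The strongest reply is that the article never says a null result will count as proof of safety, and that it cautions against firm conclusions in both the abstract and the main Discussion. That stands. A reader might infer that a non-significant test *would* be reported as confirming safety, but the documents support only that it *could* be misread that way. The cautions still do not settle the matter, since neither says which hypothesis is under test or how non-significance will be interpreted.

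A reader might also infer that all three hypotheses contradict the caption. They do not. The caption's sentence does not name tumour markers, and the Introduction describes a marker rise on a GLP-1 RA with no neoplasm found, so H2 and the caption can both be true. H3 has no direction, and a difference could arise from IPMN status or from a lower incidence with exposure.

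Two further replies are partly right. The Fig 1 graphic is not available here, so the point rests on the caption, but the caption sentence is complete and conflicts with H1 by itself. The absence of a margin or an interval rule is not a fault in its own right, because a separate analysis plan may supply it. Two opposite statements in the same article are not explained by condensation. Low power is likewise a separate matter and is partly acknowledged; here it only shows how likely the ambiguous result is.

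**Conclusion.** The point holds for the primary outcome. The hypothesis declared through Fig 1 and the hypothesis tested under H1 are opposites, and the planned test cannot support the declared one. H3 is in tension with the caption, and H2 is not clearly covered by it. This conclusion depends on no assumed rate.

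The size is illustrative and rests on assumed progression risks and a one-sided alpha of 0.05. A true doubling from 20% to 40% gives a non-significant result about 75% of the time at 10 per group and 59% at 20. Across the four scenarios the range is 72% to 87% at 10 per group and 51% to 77% at 20. Equal observed risks of 20% leave differences of about ±34 or ±25 points within the 95% interval. A non-significant result would therefore say little about safety. The documents do not show that the investigators intend to claim otherwise.

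**What to change.** State one hypothesis set, in the same terms, in the Fig 1 caption and the Analysis plan. The article does not show which direction was intended, so the investigators must choose before seeing results:

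- **Keep the planned test.** Null: no increase in progression with GLP-1 RA. Alternative: more progression. Reword the caption to match.
- **Keep the no-increase hypothesis.** Pre-specify a margin and judge the upper confidence limit against it. Even a 20-point margin needs 28 to 65 per group in the scenarios above, so 10 to 20 per group is unlikely to suffice.

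Under either choice:

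- Say whether the caption's hypothesis covers tumour markers and AP, and word H2 and H3 consistently with it.
- Report the risk difference with an interval whose level matches the test: a two-sided 95% interval with a two-sided 0.05 or one-sided 0.025 test, or a 90% interval with a one-sided 0.05 test. Otherwise a significant one-sided 0.05 result could sit beside a 95% interval that includes zero.
- Add a sentence such as: a non-significant result will not be interpreted as absence of association or as evidence of safety.

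Keeping the planned test costs edits to the caption and the Analysis plan plus one interval, with no new patients or data. The margin route would need a larger sample.

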### Population

Inclusion criteria are adult patients (≥18 years old) with a radiological diagnosis of IPMN and/or documented treatment with GLP-1 RAs, availability of medical records including laboratory results and imaging studies and signed informed consent permitting the use of anonymized clinical data for research. Eligible individuals will then be classified into one of four groups:

Patients with GLP-1 RA exposure and IPMNPatients with GLP-1 RA exposure without IPMNPatients without GLP-1 RA exposure with IPMNPatients without GLP-1 RA exposure and without IPMN = general population

Exclusion criteria is refusal of consent for research participation.

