### Radiological evaluation

MRI is the preferred imaging modality; CT scans will be included if MRI is unavailable. Two senior radiologists at HFR will independently and blinded to prior findings assess imaging studies with the internationally recognized semiological criteria for assessing cystic pancreatic lesions on cross-sectional imaging: high-risk stigmata and worrisome features (cyst diameter, enhancing mural nodules, thickened or enhancing cyst walls, main pancreatic duct diameter, change in calibre, lymphadenopathy, cystic growth). In addition, morphological and signal analysis criteria of the pancreatic gland will be analysed (glandular volume, T1 and T2 weighted signal, diffusion restriction). Furthermore, radiological assessments will be used to monitor for any signs of pancreatitis, such as pancreatic inflammation or fluid collections, that may be associated with GLP-1 RA therapy.

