#### Positive controls.

Groups need to balanced in age, BMI, and in their number of follow-ups. If age between groups is unbalanced, as defined by a Cohen’s d > 0.4, outliers will be removed until this threshold is reached. For the number of follow-ups, follow-ups above the limiting factor will be ignored from the data collection to balance the groups if needed.

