## Discussion

This study aims to provide preliminary insights into the potential impact of GLP-1 RAs therapy on the progression and clinical outcomes of IPMNs. A better understanding of the relationship between GLP-1 RA exposure and IPMNs may help address current safety uncertainties and support clinical decision-making in this complex patient population.

Several limitations must be acknowledged. The retrospective design introduces inherent risks of selection and information bias, while the relatively small sample size limits statistical power and the ability to detect modest associations. Patient identification may be incomplete, as GLP-1 RAs prescriptions may have been initiated by healthcare providers outside the participating institutions or inconsistently documented and therefore not fully captured in institutional records. Furthermore, initiation of the treatment may have been influenced by clinical judgement and recent literature implying a possible link between GLP1 Ras use and pancreatitis or pancreatic cancer, introducing potential prescription bias. In addition, the relatively recent and rapidly increasing widespread use of GLP-1 receptor agonists may limit the ability to assess long-term effects on IPMN evolution. As a result, potential late modifications or clinically relevant changes may not yet be detectable within the available follow-up period.

Therefore, the results should be interpreted as hypothesis-generating. Despite these limitations, this study addresses an important gap in the current literature and may serve as a basis for future prospective, multicentre studies.

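### Unexposed IPMN controls are drawn and balanced without regard to duct type, which the protocol links to malignant potential, so the unadjusted H1 comparison can be confounded in either direction

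*Protocol article*

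**What the plan says.** **Selection of controls.** Under Study design (text after the Fig 1 legend), patients with both IPMN and GLP-1 RA treatment are found by crossing List A (IPMN) with List B (GLP-1 RA). Then "The same number of patients will be randomly extracted from the two lists", with a worked example for one hospital, and "The same procedure will be carried out for the other two institutions". Hospital is the only stratum.

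**Eligibility.** The Population section admits adults "with a radiological diagnosis of IPMN and/or documented treatment with GLP-1 RAs". It does not restrict by duct type or baseline lesion features.

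**Balance.** Under Positive controls: "Groups need to balanced in age, BMI, and in their number of follow-ups". No lesion characteristic is on this list.

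**Primary test.** In the Analysis plan, H1 reads "We expect significantly more occurrences of change in at least one of the criteria from the Kyoto 2023 Consensus" in exposed than in unexposed IPMN patients. The test is a one-sided comparison of two proportions with no covariate or stratum. The Sampling plan expects 10 to 20 exposed IPMN patients and the same number of unexposed ones.

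**Lesion type and prescribing.** The Introduction calls IPMNs "notable for their potential to progress to malignancy, particularly in main-duct subtypes". The Discussion says that "initiation of the treatment may have been influenced by clinical judgement and recent literature implying a possible link" with pancreatitis or pancreatic cancer, and calls this a potential prescription bias.

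**The concern.** A confounder needs a link to outcome and a link to exposure. The protocol supplies material for both. Duct type bears on malignant potential, and prescribers worried about the pancreas may have decided whom to treat with the pancreas in mind. Duct type nevertheless appears nowhere in eligibility, in the draw, in the balance rule or in the H1 test.

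This differs from confounding by diabetes or obesity. It concerns the lesion that the primary outcome measures. If the exposed group holds a different share of main-duct lesions from the List A draw, the difference in Kyoto-criteria changes mixes lesion type with drug effect. The study is meant to inform the safety of these drugs in IPMN, so both errors matter: a false signal of harm, and a real harm hidden by a quieter set of exposed lesions.

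The draw is the right place to act. With 10 to 20 patients per group, later adjustment can do little to repair a poor set of controls.

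**Working it through.** **Plan's own figure.** The protocol gives no lesion mix and no change risk by lesion type, so there is nothing to reproduce. The risks and mixes below are assumptions.

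**Step 1. Expected proportions with no drug effect.** Let s be the share of higher-risk lesions in a group, h the risk of a Kyoto-criterion change in those lesions and l the risk in the others. Then p = s × h + (1 − s) × l. With h = 0.60 and l = 0.25:

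- Exposed, s = 0.10: 0.10 × 0.60 + 0.90 × 0.25 = 0.285
- Unexposed, s = 0.30: 0.30 × 0.60 + 0.70 × 0.25 = 0.355

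The difference is −7.0 points, or 0.7 patients at n = 10 and 1.4 at n = 20. The standard error, √[p1(1 − p1)/n + p0(1 − p0)/n], is about 21 points at n = 10 and 15 at n = 20.

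**Step 2. What H1 does with these proportions.** Rejection rate of the one-sided pooled z test at 0.05, by exact enumeration of two independent binomials:

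| Exposed vs unexposed | n = 10 per group | n = 20 per group |
|---|---|---|
| 35.5% vs 35.5% (same mix) | 5.3% | 4.9% |
| 28.5% vs 35.5% (10% vs 30% higher-risk) | 2.4% | 1.8% |
| 35.5% vs 28.5% (30% vs 10% higher-risk) | 9.6% | 12.3% |

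**Step 3. Range over other assumptions, still with no drug effect.** Three pairs of change risks were used (50% and 15%, 60% and 20%, 40% and 20%):

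| Higher-risk share, exposed vs unexposed | n = 10 | n = 20 |
|---|---|---|
| 40% vs 20% | 7–10% | 9–14% |
| 50% vs 20% | 9–14% | 12–20% |
| 20% vs 40% or 50% | 1–3% | 1–3% |

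**Step 4. Masking of a real harm.** Suppose the drug adds 25 points to the change risk in every lesion. With the same mix (60.5% vs 35.5%), power is 33% at n = 10 and 45% at n = 20. With quieter exposed lesions (28.5% + 25 = 53.5% vs 35.5%), it falls to 22% and 28%.

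**Step 5. Chance imbalance.** If 30% of lesions are higher-risk in both sources, the groups differ by at least 20 points in 46% of draws at n = 10 and 23% at n = 20. If 20% are, the figures are 39% and 16%. The first row of Step 2 shows that this leaves the error rate near 5%. It is sampling variation that the test already allows for.

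**Step 6. Which baseline can be used.** The Analysis plan sets T0 in exposed patients at the first follow-up examination after GLP-1 RA initiation. A feature seen at T0 may therefore have arisen on treatment. Crossing hospital (3), type (2) and feature status (2) would also give 12 cells for 10 to 20 exposed patients. Hospital by type gives 6.

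**The case against.** The strongest reply has four parts.

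**The link to the outcome is partly inferred.** The Introduction speaks of progression to malignancy, not of change in a Kyoto criterion, which is the H1 event. This stands as a limit: duct type is the one lesion feature with direct support in the text. A reader might infer that baseline worrisome features also drive the later course. The Radiological evaluation section only lists them as items to read ("high-risk stigmata and worrisome features (cyst diameter, enhancing mural nodules, thickened or enhancing cyst walls, main pancreatic duct diameter", and others), so that remains an inference.

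**The direction is not given.** A reader might infer that prescribers avoided risky lesions and that the bias must make the drug look safe. The Discussion mentions clinical judgement and literature on pancreatitis and cancer; it does not mention duct type or lesion features. H1 is also a test for excess change with no non-inferiority margin, so a non-significant result would not establish safety.

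**Large chance imbalances are not bias.** A reader might take the 46% and 23% figures as evidence of a biased design. Step 5 shows that they are not. Bias needs a systematic difference between exposed and unexposed lesions.

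**The protocol discloses the problem.** It concedes selection and prescription bias and calls its results hypothesis-generating, and adjusted analyses may sit in a plan not shown. Disclosure tempers the claims but does not control the confounder. The sampling rule and balance list are stated positively and fixed here, and a later analysis plan cannot change which controls were drawn.

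**Conclusion.** The point holds for duct type. The protocol names a lesion characteristic with a bearing on malignant potential, accepts that prescribing may have been selective because of feared pancreatic harm, and then draws and balances controls without that characteristic ahead of an unadjusted primary test.

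The size depends on inputs that the documents do not give. On the assumptions shown, a 20-point difference in lesion mix shifts the H1 contrast by 4 to 8 points and moves its rejection rate from 5% to about 2–3% or to about 7–14%, depending on direction. That shift is small against a standard error of 15 to 21 points, but it is systematic and more patients would not remove it. The documents support neither a direction nor a claim that the random draw is biased by chance imbalance. The change should be made before controls are extracted.

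**What to change.** 1. **Study design, extraction from List A.** Draw the unexposed IPMN controls at random within hospital and IPMN type (main-duct or mixed versus branch-duct), in the same numbers as the exposed patients. Take type from existing radiology reports. Where a hospital has no control of the required type, draw one of that type from another hospital and report it.
2. **Positive controls.** Add IPMN type to the balanced features, and state that balance comes from the draw. The section's present tools (removing age outliers, ignoring surplus follow-ups) do not suit a binary feature, and deletion would shrink a small sample.
3. **Worrisome features and high-risk stigmata.** Do not match on their T0 status, because that could match away a drug effect. Report them by group, from the last imaging before GLP-1 RA initiation in exposed patients and from the first imaging in controls.
4. **Analysis plan.** Add a descriptive H1 result by IPMN type, stating that 10 to 20 per group allows no formal subgroup conclusion.

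**Cost.** Protocol wording, a pre-screen of List A reports for IPMN type before extraction, and an occasional control from another hospital. Some older reports may not state type clearly. No extra patients are needed.
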